## Abstract

**Background:**

Health worker compliance with established best-practice clinical and public health guidelines may be enhanced by customized checklists of care and clinical decision support driven by point-of-care data entry into an electronic health registry. The public health system of Palestine is currently implementing a national electronic registry (eRegistry) for maternal and child health. This trial is embedded in the national implementation and aims to assess the effectiveness of the eRegistry’s interactive checklists and clinical decision support, compared with the existing paper based records, on improving the quality of care for pregnant women.

**Methods:**

This two-arm cluster randomized controlled trial is conducted in the West Bank, Palestine, and includes 120 clusters (primary healthcare clinics) with an average annual enrollment of 60 pregnancies. The intervention tool is the eRegistry’s interactive checklists and clinical decision support implemented within the District Health Information System 2 (DHIS2) Tracker software, developed and customized for the Palestinian context. The primary outcomes reflect the processes of essential interventions, namely timely and appropriate screening and management of: 1) anemia in pregnancy; 2) hypertension in pregnancy; 3) abnormal fetal growth; 4) and diabetes mellitus in pregnancy. The composite primary health outcome encompasses five conditions representing risk for the mother or baby that could have been detected or prevented by high-quality antenatal care: moderate or severe anemia at admission for labor; severe hypertension at admission for labor; malpresentation at delivery undetected during pregnancy; small for gestational age baby at delivery undetected during pregnancy; and large for gestational age baby at delivery. Primary analysis at the individual level taking the design effect of the clustering into account will be performed as intention-to-treat.

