
### Objectives

#### Primary objectives

To estimate the effectiveness of the eRegistry’s interactive checklists and clinical decision support on: 1) improving the provision of timely and appropriate screening and management for important conditions during ANC; and 2) health outcomes for the mothers and the newborns.

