### Outcomes

The focus of the outcome measures have been informed by national stakeholder consultations as representing key areas of quality concern in the Palestinian context, and to serve as sentinel outcomes for the overall quality of care. The adverse pregnancy outcomes reflect conditions that put the baby and/or mother at risk during labor or after delivery, and that could or should have been identified and/or managed prior to labor and delivery. The process (adherence) outcomes (Table 2) for the screening and management of the risk conditions and the corresponding adverse pregnancy outcomes (Table 3) will be assessed as primary outcomes. We have defined indicators to measure the process (adherence) outcomes (Additional file 1) based on the current guideline-based algorithms for management of conditions during ANC in Palestine (Additional file 2). Secondary outcomes are given in Table 4.

**Table 2 Tab2:** Primary process (adherence) outcomes, source of data, measurement sequence, and definitions

Process (adherence) outcomes	Source of data	Measurement sequence	Definitions
Timely and appropriate screening and management of anemia during pregnancy	Case records data from the PHC in the eRegistry	Registrations continuously at point of care, data export to the trial monthly	Proportion of women attending ANC who receive: 1. anemia screening at booking, and 2. screening at any ANC visits at 24 and 36 weeks if no anemia detected, and 3. rescreening after 1 month if mild or moderate anemia is detected, and 4. referred to high-risk clinic if refractory mild or moderate anemia is detected, and 5. referred to hospital if severe anemia is detected.
Timely and appropriate screening and management of hypertension in pregnancy	Case records data from the PHC in the eRegistry	Registrations continuously at point of care, data export to the trial monthly	Proportion of women attending ANC who receive: 1. blood pressure measurement at booking visit, and 2. blood pressure measurement at every ANC visit, and 3. appropriate laboratory tests for mild hypertension, and 4. referred to high-risk clinic hospital for chronic or gestational hypertension, and 5. referred to hospital for hypertension with proteinuria or signs of eclampsia.

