Timely and appropriate screening and management of abnormal fetal growth	Case records data from the PHC in the eRegistry	Registrations continuously at point of care, data export to the trial monthly	Proportion of women attending ANC who receive: 1. first fundal height measurement at 16–20 weeks, and 2. fetal growth monitoring at every ANC visit, and 3. referred to ultrasound if discrepancy between fundal height and gestational age, and 4. referred to high-risk clinic if ultrasound confirmed fetal growth restriction.
Timely and appropriate screening and management of diabetes in pregnancy	Case records data from the PHC in the eRegistry	Registrations continuously at point of care, data export to the trial monthly	Proportion of women attending ANC who receive: 1. diabetes screening at booking, and 2. screening with random blood sugar test at 24–28 weeks, and 3. referred to high-risk clinic if random blood sugar test or glucose challenge test ≥ 140 mg/dl.

*ANC* antenatal care, *eRegistry* electronic registry, *PHC* primary healthcare clinics

**Table 3 Tab3:** Primary adverse pregnancy outcomes, source of data, measurement sequence, and definitions

Adverse pregnancy outcomes	Source of data	Measurement sequence	Definitions
Moderate or severe anemia at admission for labor	Hemoglobin admission data from hospitals in the eRegistry (public, private, and NGO hospitals)	Registrations continuously at point of care, data export to the trial monthly	Moderate anemia: hemoglobin greater than 7 and less than 9 g/dl; severe anemia: hemoglobin < 7 g/dl
Severe hypertension at admission for labor	Blood pressure admission data from hospitals (public, private, and NGO hospitals) in the eRegistry	Registrations continuously at point of care, data export to the trial monthly	Severe hypertension: systolic blood pressure ≥ 160 mmHg and/ or diastolic blood pressure ≥ 110 mmHg
Malpresentation at delivery undetected during pregnancy	Presentation at delivery data from hospitals (public, private, and NGO hospitals) in MCH registry	Registrations continuously at point of care, data export to the trial monthly	All non-cephalic presentations at or after 36 weeks of gestation and at labor
Small-for-gestational age baby at delivery undetected during pregnancy	Birth weight data from hospitals (public, private, and NGO hospitals) in the eRegistry	Registrations continuously at point of care, data export to the trial monthly	Small for gestational age: less than 2549 g [34]

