### Sample size

Sample size calculations for primary outcomes were performed in STATA (StataCorp. 2015, Stata Statistical Software: Release 14; College Station, TX, USA) “clustersampsi” using a 5% significance level and an assumed a priori intracluster correlation coefficient (ICC) of 0.01 for adverse pregnancy outcomes and 0.04 for the process outcomes [27]. Table 5 shows the estimated prevalence of primary outcomes for sample size calculations. We made sample size calculations to achieve a power of 90% based on an estimated average number of new pregnancies for 8 months in the study PHC. With 120 clusters recruiting for 8 months (with a minimum average cluster size of 44 in the year 2013), we will have more than 90% power to detect a relative 25–30% change in the composite adverse pregnancy outcome. With this sample size, we will have more than 90% power to detect a 15–25% change in the process primary outcomes. Effects of clustering and unequal cluster sizes have been accounted for in the sample size calculations (design effect = 1.75 for adverse pregnancy outcomes and 3.99 for process outcomes, and coefficient of variation of cluster size = 0.85) [28].

**Table 5 Tab5:** Assumed prevalence for primary outcomes for calculations of sample size

Outcome measure	Control group prevalence
Adverse pregnancy outcomes: composite of any of the five conditions below, accounting for coexistence of conditions in 10% of women	0.145
1. Moderate or severe anemia at admission for labor	0.0225
2. Large-for-gestational age baby at delivery	0.054
3. Small-for-gestational age baby at delivery undetected during pregnancy	0.057
4. Malpresentation at delivery undetected during pregnancy	0.02
5. Severe hypertension at admission for labor	0.01
Process (adherence) outcomes	0.40–0.60

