## Discussion

Electronic health information systems and programs are frequently tested in isolation, often as pilots or with less robust study designs [31]. This CRCT aims to contribute to filling this evidence gap. In order to study effectiveness of the intervention in the health system, we have designed a pragmatic CRCT. We have worked closely with the Palestinian MoH to plan the intervention and the timelines for the implementation of the eRegistry. All our communication strategies to the study clinics have always been through the Palestinian MoH via established channels within the health system in an attempt to keep monitoring of sites robust but as close to real-world settings as possible. We have striven to maintain generalizability of study findings by including a large representative sample of PHC and having no individual-level eligibility criteria. Data for outcome measures are derived from existing data collection pathways for the eRegistry in Palestine. The design and implementation of this CRCT places emphasis on the outcomes, as well as the feasibility of their measurement, in registry settings within the health system. Loss to follow-up is expected to be minimal since all our data sources are part of the eRegistry. We have designed outcome measures to directly reflect the effect of the intervention within the setting of an electronic registry, justifying the use of secondary data, where the process outcomes are based on the care providers’ own documentation of process, and health outcome measures are based on data collected independently from the care provider.

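### Two of the five components of the primary health composite are named as undetected conditions but defined without a detection criterion; if the names govern, better recording alone could produce the target effect

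*Protocol article*

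**What the plan says.** Primary objective 2 concerns "health outcomes for the mothers and the newborns". The abstract describes the endpoint for it as follows: "The composite primary health outcome encompasses five conditions representing risk for the mother or baby that could have been detected or prevented". Two of the five conditions are "malpresentation at delivery undetected during pregnancy; small for gestational age baby at delivery undetected during pregnancy". Table 3 repeats the qualifier ("Small-for-gestational age baby at delivery undetected during pregnancy"), and so does Table 5 ("4. Malpresentation at delivery undetected during pregnancy"). The other three conditions (anemia, severe hypertension, large for gestational age) count whenever they occur.

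The definition column of Table 3 says something different. It takes malpresentation as every non-cephalic presentation from 36 weeks on and at labor, and small for gestational age as a birth weight under 2549 g. Both are sourced from hospitals. Neither definition mentions antenatal detection.

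The Blinding section says that hospital staff collect the adverse outcomes in a system not linked to the eRegistry. The Discussion adds that "health outcome measures are based on data collected independently from the care provider".

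**The concern.** There are two linked problems.

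First, the primary outcome is not fixed. Under the names, a small or malpresenting baby leaves the composite once it counts as detected before delivery. Under the Table 3 definitions it stays in. These are different endpoints with different control prevalences, and Table 5 labels its figures with the undetected version.

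Second, if the names govern, the composite adds failures of detection (two components) to occurrence of conditions (three components). The intervention prompts providers to look for and record such conditions. A fall in the composite could then reflect better detection, fewer affected women, or both, and would be reported as effectiveness under a health-outcome objective.

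Detection status cannot come from the hospital alone. It has to be read from the antenatal record, which is entered at the point of care in the intervention arm and computerized from completed paper files in the control arm (Data extraction methods). A difference in recording between arms could move these two components, and the claimed independence from the care provider would not cover them.

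**Working it through.** **Inputs.** From Sample size and Table 5: control composite 0.145; anemia 0.0225; large for gestational age 0.054; small for gestational age undetected 0.057; malpresentation undetected 0.02; severe hypertension 0.01; 120 clusters, mean size 44; ICC 0.01; coefficient of variation of cluster size 0.85; 5% level. From Allocation: 1:1. From Statistical methods: two-sided tests.

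**Reproducing the plan's figures.**
- Design effect = 1 + ((1 + CV²) × m − 1) × ICC = 1 + (1.7225 × 44 − 1) × 0.01 = 1.748, against the stated 1.75.
- Effective size per arm = 60 × 44 / 1.748 = 1510.
- Normal-approximation power for two proportions from 0.145: 85.0% for a 25% relative reduction, 90% at 26.9%, 95.4% for 30%. The 90% point lies inside the stated 25–30% range, although the 25% end falls short of it.

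**Weight of the two components.**
- Component sum = 0.0225 + 0.054 + 0.057 + 0.02 + 0.01 = 0.1635.
- Detection-dependent part = 0.057 + 0.02 = 0.077, and 0.077 / 0.1635 = 47%.
- With every component shrunk in proportion so that the sum matches the composite (0.145 / 0.1635 = 0.887), this part is 0.077 × 0.887 = 0.068.

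**Share of missed cases that must be recorded as detected, all conditions unchanged.** The target falls are 0.25 × 0.145 = 0.03625 and 0.30 × 0.145 = 0.0435.

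| Treatment of overlap | Detection-dependent part | 25% target | 30% target |
|---|---|---|---|
| No scaling | 0.077 | 0.03625 / 0.077 = 47% | 0.0435 / 0.077 = 56% |
| Proportional scaling | 0.0683 | 0.03625 / 0.0683 = 53% | 0.0435 / 0.0683 = 64% |

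The documents do not say which conditions coexist. If all the overlap (0.1635 − 0.145 = 0.0185) fell on these two components, their part would be 0.077 − 0.0185 = 0.0585, and the shares would rise to about 62% and 74%.

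**Illustration only.** If half of the missed cases were recorded as detected, under proportional scaling, the composite would go from 0.145 to 0.145 − 0.5 × 0.0683 = 0.111 (risk ratio 0.765, a 24% reduction). With 1510 effective women per arm, power to find that difference is about 80%.

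**Under the Table 3 definitions taken literally**, detection does not enter and none of these shifts can occur.

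**The case against.** The strongest reply is that the Table 3 definitions already are an occurrence endpoint from hospital data, and that the Blinding and Discussion statements fit them. This is correct as far as it goes. But the undetected wording stands in the abstract, in Table 3 itself and in the Table 5 prevalences used for the sample size, so the definitions cannot simply be taken to prevail. What remains is a conflict that the protocol has to resolve.

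A second reply is that detection is intended and disclosed: the abstract speaks of conditions detected or prevented, and the Outcomes section of conditions "that could or should have been identified and/or managed prior to labor and delivery". This also stands. Arriving in labor with an unrecognized risk is a legitimate thing to measure in a trial of care quality, and the composite need not be abandoned. The difficulty is the health-outcome label when detection and occurrence are not kept apart.

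Three stronger readings are tempting, and the documents do not support them.
- A reader might infer that any suspicion in the record removes a case, so that flagging every fetus would score zero. No section says that suspicion counts as detection. The fetal-growth process outcome in Table 2 refers to ultrasound confirmation, and a rule requiring confirmation would block that route.
- A reader might infer that the trial could not tell more detection from fewer affected women. Statistical methods plans a table that includes birth weight and presentation at term, and an analysis of the probability that affected women are identified and managed. Hospital data are merged by the mother's identifier. The material for separation exists; what the article does not state is an occurrence version of the composite beside the named one.
- A reader might take the 80% figure as the chance of a spurious health finding. It follows from an arbitrary halving, and the documents give no expected gain in detection.

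Finally, supportive analyses may sit in an analysis plan that is not shown. That answers a complaint of omission, but not a conflict inside the stated definition of a primary outcome.

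**Conclusion.** The point holds as a conflict in the definition of the primary health composite and, if the component names govern, as a mixture of detection with occurrence. In that case 47% of the component sum depends on detection, and recording about 47% to 64% of missed cases as detected would reach the full 25–30% target with no condition changed. The range assumes either no scaling or proportional scaling for coexisting conditions, and it is a threshold only. The stated independence from the care provider then does not extend to these two components. It does not follow that an observed fall would be artefactual or that earlier detection is worthless. What follows is that such a fall could not, by itself, be read as improved health of mothers or newborns.

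**What to change.** 1. Reconcile the component names with the Table 3 definitions. If the undetected qualifier is kept, state the rule for detection (what entry counts, and by when) and its source in each arm, and qualify the independence statements in Blinding and Discussion for these two components.
2. Keep the composite, and prespecify beside it an occurrence version with the same five conditions, counting small for gestational age and malpresentation from hospital data whether or not detected.
3. Report by arm the proportion of women flagged for each of the two conditions, including flags not confirmed at birth.
4. State in advance that, if only the detection-dependent version falls, the result will be described as fewer undetected or unprevented risks at delivery and not as improved health outcomes.

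The cost is some wording and one extra derived variable from hospital data already collected. The claim under objective 2 may become narrower. The total prevalence of the two conditions, detected or not, is not given, so the power of the occurrence version cannot be computed from the documents. It should therefore inform interpretation and not serve as a formal gate.

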**Discussion:**

This trial, embedded in the national implementation of the eRegistry in Palestine, allows the assessment of process and health outcomes in a large-scale pragmatic setting. Findings will inform the use of interactive checklists and clinical decision support driven by point-of-care data entry into an eRegistry as a health systems-strengthening approach.

**Trial registration:**

ISRCTN trial registration number, ISRCTN18008445. Registered on 6 April 2017.

**Electronic supplementary material:**

The online version of this article (doi:10.1186/s13063-017-2386-5) contains supplementary material, which is available to authorized users.

## Background

Monitoring progress in universal health coverage requires reliable data that sufficiently depict the quality of health services and complexities of health systems [1]. The availability of relatively well-defined interventions and measurement indicators for reproductive, maternal, newborn and child health (RMNCH) provides a head start in monitoring and, ultimately, achieving universal health coverage within this sphere [2]. To enhance the quality of care in RMNCH in low- and middle-income settings, implementation of innovative health system interventions should be prioritized [3]. Checklists and clinical decision support for care providers are tools that can enhance quality of healthcare service delivery. Checklists support implementation of interventions and protocols at all levels of a health system among all care providers in a cadre, and have the ability to standardize decision-making throughout the health system [4–6]. The World Health Organization 29-item ‘Safe Childbirth Checklist’, designed to facilitate childbirth protocols, has been demonstrated to improve provision of safe practices by health workers and the quality of care [7, 8]. Interactive checklists on electronic platforms can provide decision and guideline support in response to structured data entry by care providers at the point-of-care (Table 1). Interactive checklists and clinical decision support, as compared to static checklists, have the advantage of offering individual case-based management suggestions [9]. When data entry is made online into a centralized electronic registry (eRegistry), the system not only supports the quality of care delivered by the individual care provider at one specific patient contact, but also supports the patient-centered continuity and quality of care along and across the health system [10]. The interactivity in the checklists, customized to health workers and their setting and level of health system, may form an important tenet for its effective use. Point-of-care support tools for health workers can help overcome frequent barriers to high-quality clinical care, such as the lack of accessible guidelines and validated management suggestions [11]. Interactive checklists and clinical decision support can potentially strengthen health workforce capacity and thus contribute to strengthening universal health coverage. Studies on electronic health (eHealth) and mobile health (mHealth) report good potential for such tools [12–14], and in the RMNCH field they may facilitate healthcare practice, health communication, and health education [15, 16]. Health systems may be made more effective, efficient, and accountable by exploiting opportunities of communications enabled by health information systems. However, robust research and evidence evaluating such interventions are scarce [17]. A systematic review of randomized controlled trials (RCTs) to study the effectiveness of any form of clinical decision support system linked to electronic health records showed a moderate effect on morbidity [18]. Most large RCTs for electronic health information systems, clinical decision support systems, and electronic registries have been conducted in high-income countries, with obviously different contextual considerations [19]. Implementing clinical decision support tools and electronic registries is resource-intensive, and substantial efforts are required in design, implementation, training, and support [20]. Considering this, there is a need for RCTs of the health systems to justify the extent of use of e- and mHealth solutions in low- and middle-income countries, particularly in primary healthcare where there is the most relevant demand for evidence [21].

**Table 1 Tab1:** List of working definitions describing different components constituting intervention and the delivery platform

Term	Working definition
eRegistries	Electronic registries (eRegistries) are systems using information and communication technologies for the systematic longitudinal collection, storage, retrieval, analysis, and dissemination of uniform information on health determinants and outcomes of individual persons, to serve healthcare services, health surveillance, health education, knowledge, and research [10].
Interactive checklists	Interactive checklists are checklists delivered on electronic platforms. eRegistry’s interactive checklists integrate individualized decision support for daily clinical procedures, diagnosis, management, and referral routines in response to systematic point-of-care data entry by healthcare providers [10].
Clinical decision support system	An electronic system designed to aid directly in clinical decision making, in which characteristics of individual patients are used to generate case-specific assessments or recommendations that are then presented to clinicians for consideration [33].

